### Data collection and statistical analysis

#### Sample size

Based on a large study among 2800 hematologic patients [6], we expect an additional increase of 5 points, with a standard deviation of 7 points, in the QLQ-C30 score of the experimental group (HRVB+APA) after the 12-week intervention. Due to an estimated 10% missing data rate and dropout rate (abandonment, death, loss of sight), we aim to include 70 patients in the protocol (Fig. 3). They will be randomly assigned to one of two treatment groups (HRVB+APA (*n* = 35) versus APA only (n = 35)). Sample size was calculated with PASS 11® software (power analysis and sample size) to show a significant difference in improvement of quality of life in the experimental group with an alpha level of 5% and a statistical power of 80%.

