#### Statistical analysis

To evaluate effectiveness of HRVB, we will compare the average evolutions (T3-T1 difference score) between the experimental group (HRVB+APA) and the control group (APA). Student’s t-test will be performed for the different dimensions and scale sub-scores of each questionnaire, as well as cardiac coherence score and SDNN. An analysis of longitudinal data collected at T1, T2, T3 and T4 will be conducted using a linear mixed model with structured covariance residuals. The bivariate survival analysis (death and / or relapse, survival without serious infectious events) will be carried out using the Kaplan-Meier method. Group comparison will be calculated using the log-rank test.

All hypotheses will be tested in a single analysis, intention to treat (according to the group assigned by the randomization), bilaterally at the threshold α = 5%. The analyses will be performed with SAS® (version 9.4, SAS Institute Inc., Cary, NC, USA). At the end of the research study, investigators will anonymize the collected data and results will be submitted to the research partners. The statistician, methodologist and investigators will have access to the final dataset. An article in a journal indexed on Medline will be carried out in post-trial.

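### The T3-T1 t-test that judges effectiveness omits patients without a T3 score, and the planned mixed model that would retain their data is not given the deciding role

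*Protocol article*

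**What the plan says.** All of this is in the protocol article.

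- **Effectiveness comparison (Statistical analysis):** "we will compare the average evolutions (T3-T1 difference score) between the experimental group (HRVB+APA) and the control group (APA"). The test is named next: Student's "t-test will be performed for the different dimensions and scale sub-scores of each questionnaire, as well as cardiac coherence score and SDNN". No baseline adjustment and no rule for a missing T3 are given.
- **Longitudinal model (same section):** "An analysis of longitudinal data collected at T1, T2, T3 and T4 will be conducted using a linear mixed model with structured covariance residuals". The structure is not named, and the model's rank relative to the t-test is not stated.
- **Analysis principle (same section):** "All hypotheses will be tested in a single analysis, intention to treat (according to the group assigned by the randomization"), two-sided at 5%.
- **Expected loss (Sample size):** "Due to an estimated 10% missing data rate and dropout rate (abandonment, death, loss of sight), we aim to include 70 patients". The target is given as "we expect an additional increase of 5 points, with a standard deviation of 7 points, in the QLQ-C30 score of the experimental group", "with an alpha level of 5% and a statistical power of 80"%.

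**The concern.** A T3-T1 difference does not exist for a patient who has no T3 assessment. Unless missing values are filled in, that patient drops out of the test that judges effectiveness, even when a T2 score was collected at week 6. The 10% allowance in the sample size protects power. It does not protect against bias if those who leave differ from those who stay.

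The design makes unequal loss foreseeable. Only the HRVB arm has ten additional supervised one-hour sessions and 20 minutes of daily home practice (HRVB training section). If patients who feel no benefit are the ones who give up that extra burden, the remaining HRVB patients look better than the arm as randomised. The documents neither state nor exclude this, so it is an assumption.

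The mixed model also yields a group contrast at T3 and can use the T1 and T2 scores of patients lost later. With no explicit ranking, two results for the same question could disagree, and the choice between them would remain open after the data are seen.

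**Working it through.** **1. Reproduce the plan's sample size.** Inputs from the Sample size section: difference 5, SD 7, two-sided alpha 5%, power 80%, loss 10%.

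n per arm = 2 × (1.96 + 0.84)² × 7² / 5² ≈ 2 × 7.85 × 1.96 ≈ 30.8, so 31. Inflated: 31 / 0.90 = 34.4, so 35 per arm and 70 in total, as stated. (With the exact t distribution: 32 per arm, 32 / 0.90 = 35.6, so 36 per arm and 72 in total, close to 70.)

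The trial is therefore sized for a test on about 62 or 63 patients (2 × 31 = 62; 70 × 0.90 = 63). Power at 31 per arm is 0.80 (normal) or 0.79 (t). With all 35 per arm it would be 0.85 or 0.84. The sample size is not in error.

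**2. Size of a possible bias, in closed form.** Let d be the proportion lost in an arm and G the amount by which completers' mean change exceeds that of the patients lost. The completer mean then exceeds the full-arm mean by d × G, and the bias of the group difference is d(HRVB) × G(HRVB) − d(APA) × G(APA). With the same G in both arms, assumed to be 5 to 10 points:

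| Loss HRVB / APA | Bias (points) |
|---|---|
| 10% / 10% | 0 |
| 15% / 5% | 0.10 × 5 to 0.10 × 10 = 0.5 to 1.0 |
| 20% / 0% | 0.20 × 5 to 0.20 × 10 = 1.0 to 2.0 |

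**3. Simulation under no true effect.** Assumptions: 35 per arm, SD of change 7, correlation 0.65 between adjacent visits and 0.5 between T1 and T3. Response-driven loss after T2 follows a logistic model with slope 1.5 per 7 points of worse T1-T2 change.

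| Scenario | t-test bias | Type I error |
|---|---|---|
| 14% response-driven in HRVB, 5% random in APA | about +0.6 | 6.3% to 6.9% across runs |
| Same response-driven mechanism in both arms, 14% / 5% | +0.36 | 5.7% |
| 10% / 10%, response-driven in HRVB only | +0.46 | – |
| 10% / 10%, same mechanism in both arms | +0.02 | 4.9% |

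In the first scenario a likelihood estimate using T1 and T2 has bias of about 0. A bias of 0.6 is 0.6 / 5 = 12% of the target. By the formula in step 2 it corresponds to lost HRVB patients changing about 0.6 / 0.14 ≈ 4.3 points less than those who stay.

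**4. Precision.** With T1-T3 correlation r and equal variances s² at the two visits, the variance of the change is 2s²(1 − r), and the residual variance after adjusting T3 for T1 is s²(1 − r²). The ratio is (1 + r)/2. At r = 0.5 the standard error is multiplied by √0.75 = 0.866.

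With 35 × 0.86 = 30.1 and 35 × 0.95 = 33.25 patients observed, the t-test standard error is 7 × √(1/30.1 + 1/33.25) ≈ 1.76. Adjustment gives 1.76 × 0.866 ≈ 1.52. Simulation agrees: about 1.75 for the t-test and 1.51 to 1.53 for the likelihood estimate. A completer-only analysis of covariance on T1 also gives 1.51 to 1.53, so practically all of the gain comes from baseline adjustment and not from recovering lost patients. The documents do not give r. At r = 0.3 the factor is √0.65 = 0.81 (1.42), and at r = 0.7 it is √0.85 = 0.92 (1.62).

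**The case against.** **Intention to treat.** A reader might infer that the t-test contradicts the plan's own principle. It does not. The article defines the term in brackets as analysis by randomised group, and a t-test by assigned arm meets that definition. The article also never says that only completers are analysed. That is inferred from a difference score with no stated imputation, and detailed missing-data rules may sit in a full protocol or analysis plan that is not shown. What stands is narrower: the test as described cannot include every randomised patient.

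**Covariance.** A reader might infer that the mixed model's covariance is restrictive. The text says only that it is structured and names no form, so it is unspecified and not shown to be wrong. A structure that follows the time between visits could suit the unequal spacing. Even compound symmetry, if correlation decayed at 0.7 to 0.9 per six weeks, would leave the T3-T1 standard error nearly right (ratio 0.996 to 1.024).

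**Ranking.** The section ties effectiveness to the T3-T1 comparison and then introduces the mixed model as a longitudinal analysis, so reading the t-test as the main analysis is natural. The reference to a single analysis may simply mean no interim look. That is fair, but no explicit ranking is given. On the natural reading, the deciding test is the one that omits the lost patients.

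**Bias.** The documents give one overall 10% and no difference between arms. With equal loss from the same cause there is no bias. This stands: the bias is conditional and modest.

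**Conclusion.** The point holds in a limited form. As written, the effectiveness test is an unadjusted comparison that leaves out about 7 of 70 randomised patients and their T2 scores. A model that would keep those data is already planned, but it has no stated deciding role.

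The bias is about 0.4 to 0.6 points, with type I error near 6%, and only if loss depends on response and differs between arms in rate or cause. It is nil if loss is random or equal in rate and cause. The reduction in standard error from about 1.75 to 1.5 assumes a T1-T3 correlation of 0.5 and is mainly due to baseline adjustment. The sample size, the analysis by assigned group and the unnamed covariance structure are not shown to be wrong. This is an improvement worth making before the data are analysed, not a flaw that undermines the design.

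**What to change.** State that the T3 group contrast from the mixed model is the single decisive analysis of the primary quality-of-life score. The wording should cover:

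- all randomised patients with any score, analysed in their assigned group;
- group-by-visit terms;
- adjustment for T1, either as a response with a common baseline mean or as a covariate;
- an unstructured covariance, which for four visits has 4 × 5 / 2 = 10 parameters.

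Keep the T3-T1 t-test as a supportive analysis and label it as based on patients with both values.

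The cost is a few sentences and slightly more programming of a model already planned. No patients or visits are added. The price in assumptions is reliance on missing-at-random given the observed scores. Patients lost before T2 contribute little beyond T1, and for patients who die the model implicitly supplies a T3 score, which the report should acknowledge.

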## Discussion

Previous studies have investigated the effectiveness of HRVB compared to physical exercise [67–69]. To the best of our knowledge, there have been no studies about the added value of HRVB on physical exercise to enhance overall quality of life. While recent studies about HRVB training have demonstrated the feasibility and the effectiveness of HRVB in chronic patients [37, 41, 42], it has not yet been done in cancer patients, namely in hematology. Most clinical studies conclude that HRVB can reduce symptomatology of chronic disease and improve HRV level, supporting our hypothesis that HRVB may be feasible and effective in recovery of hematologic patients.

We hypothesize that HRVB associated with an APA program will be more effective than an APA-only program in improving quality of life during post-treatment in adult hematologic patients and expect the following outcomes from this experimental group: i) significant improvements in overall quality of life and a reported decrease in overall fatigue, anxiety and depression; ii) increased HRV levels, reflecting a better physiological regulation through autonomic control of the heart; iii) better BMI and BP measurements; and iv) less infectious events, relapses and deaths. All of these variables should be improved between T1 and T3. The results recorded at T3 could be sustained through T4, especially if patients are persistent with their home-based practice for both cardiac coherence and physical exercise.

All participating patients will be in remission for hematologic malignancies that have required hospitalization, caused sudden disruptions to their day-to-day lives, and/or have required particular aggressive treatments with high-dose chemotherapy, affecting patients’ overall quality of life. To avoid age-related effects, we have chosen a within-subject design and will exclude patients over 70 years.

Our short-term HRV recording protocol is based on the recommendations from Task Force [70] and more recently from Laborde [57], who has suggested guidelines for psychophysiological research. Although electrocardiogram is more accurate, we use the pulse sensor to assess pulse-to-pulse interval data which accurately approximates the inter-beat interval [71]. To analyze HRV data in time-domain and frequency domain, *HRVanalysis* will be used [58].

We place particular importance on describing the intervention and detailing how it will proceed to identify modalities of an effective program for assisting with cancer recovery, especially after hematologic treatments. This proceeding should enhance the implementation of a care pathway in the hematology unit at the Hospital of Reunion Island and facilitate its reproduction in other health care facilities.

In conclusion, the results of the APACCHE study should demonstrate effects of HRVB training associated with an APA program on physical functioning and emotional state in treated hematologic patients. We anticipate that overall quality of life in both psychological and physical capacities will improve. Results of this protocol will be published in the hope that our research outcomes may produce relevant knowledge about supportive cancer care in hematology and may infer new perspectives in psychophysiological research in cancer.

## Data Availability

After the completion of the current protocol, data and materials will be available from the corresponding author upon reasonable request.

## Abbreviations

APACCHE: Adapted Physical Activity and Cardiac Coherence in Hematologic patients
APA: Adapted Physical Activity
HRVB: Heart rate variability biofeedback
ANS: Autonomic nervous system
HRV: Heart rate variability
HSCT: Hematopoietic stem cell transplantation
SDNN: Standard deviation of normal-to-normal R-R interval
FFT: Fast Fourier transform
BP: Blood pressure
QLQ-C30: Quality of Life Core Questionnaire
BMI: Body mass index
LVEF: Left ventricular ejection fraction
MCID: Minimal clinically important difference
SF-36: Short-Form Health Survey
MFI-20: Multidimensional Fatigue Inventory
HADS: Hospital Anxiety and Depression Scale
GPAQ: Global physical activity questionnaire
eCRF: electronic case report form
